#### Biomarkers determination

Also, substudies on protein and genetic biomarkers will be performed following the same strategy of a case–control study nested in this cohort.

#### Follow-up neuroimaging studies

A follow-up MRI is planned after the third year of follow-up for a nested cohort of cases and controls according to the presence of silent infarcts at baseline. This will allow us to describe the incidence of new lesions.

### Data entry and monitoring

Data will be collected by investigators and supporting staff and transferred to an electronic case report form (eCRF) on a weekly basis. No personal data enabling the identification of the participants will be included in the eCRF. Previous training is warranted for all investigators before access to the live database. Data are secured from external violation by limiting access to the computer system by individual user name and password protection.

In order to minimize missing or wrong data, external monitoring for the main outcome variables is planned, including clinical and radiological variables for at least 10% of randomly selected participants.

### Statistical methods

Sample size calculation representative for our population concerning prevalence of silent infarcts has been estimated using data of population-based studies published before, which reported specific data on silent brain infarcts prevalence in participants aged 50 to 70 years old [27-30]. According to them, the expected prevalence should be about 10%. Therefore, after applying the Ene 2.0 software, with a confidence interval of 95% and an accuracy of 2%, sample size should be of at least 865 individuals, which was increased to 1000 individuals by taking into account possible losses.

Statistical analysis will be performed with the SPSS 15.0 statistical package (Chicago, Ill., USA). Statistical significance for intergroup differences will be assessed by the χ^2^ or Fisher’s exact test for categorical variables and by the T-test, ANOVA, Mann–Whitney U and Kruskal-Wallis test for continuous variables. The correlations between continuous variables will be determined with Spearman’s or Pearson’s coefficients, as appropriate. A p value <0.05 will be considered significant. Logistic regression models will be performed to identify potential predictors of silent brain infarcts and other silent lesions. Finally, Cox proportional hazards multivariate analysis will be used to identify clinical predictors of stroke/TIA or further CVE, adjusted by variables showing p values <0.1 on univariate testing. Results will be shown as OR or HR, as appropriate, with their corresponding 95% confidence intervals.

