## Abstract

**Background:**

Silent brain infarcts are detected by neuroimaging in up to 20% of asymptomatic patients based on population studies. They are five times more frequent than stroke in general population, and increase significantly both with advancing age and hypertension. Moreover, they are independently associated with the risk of future stroke and cognitive decline.

Despite these numbers and the clinical consequences of silent brain infarcts, their prevalence in Mediterranean populations is not well known and their role as predictors of future cerebrovascular and cardiovascular events in hypertensive remains to be determined.

ISSYS (Investigating Silent Strokes in Hypertensives: a magnetic resonance imaging study) is an observational cross-sectional and longitudinal study aimed to: 1- determine the prevalence of silent cerebrovascular infarcts in a large cohort of 1000 hypertensives and to study their associated factors and 2-to study their relationship with the risk of future stroke and cognitive decline.

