Regarding brain as hypertension target organ, subclinical or “silent” vascular brain lesions (i.e. infarcts, microbleeds, white matter changes) are often detected by neuroimaging in asymptomatic patients. Specifically, silent brain infarcts are five times more frequent than stroke in general population, and increase significantly both with advancing age and hypertension [3]. The term “silent” might not be entirely appropriate since these lesions could be often associated with unnoticed or subtle symptoms in patients that never asked for an evaluation, making impossible a diagnosis of stroke. The prognosis associated with these “silent” infarcts is not favourable at all, and their presence independently predicts further stroke and cognitive decline [4,5]. For all these reasons, silent brain infarcts have been recently included in the AHA Updated definition of stroke, thus emphasizing their clinical relevance [6]. This will have important consequences in public health, as it is expected to largely increase stroke prevalence. Moreover, their detection might have the potential to improve the selection of patients at higher risk for future stroke and cardiovascular events, who might benefit from more aggressive preventive treatments.

Hypertension has been related not only to the presence of silent vascular brain lesions but to the appearance of new lesions on follow-up, which can occur in up to 40%, considering progression of white matter changes [7]. Interestingly, this effect on progression is much more relevant at younger or midlife patients than later on [7,8]. Therefore, preventive strategies should pay much more attention to younger subjects, who are likely to have long term exposure to an increased risk in the following years [1].

Studies focusing on hypertensive participants have been performed, and reported a prevalence of silent brain infarcts that ranges from 20 to 86% of subjects aged 40 to 88 years old. Of note, most of these studies have included mainly Japanese populations, whereas data on Mediterranean Caucasian populations is still limited [7].

With this background, the ISSYS is designed as a cross-sectional and longitudinal study aimed to: (1) investigate the prevalence of silent cerebrovascular lesions, as signatures of brain organ damage, in a cohort of middle and advanced aged (50–70 years old) caucasian Mediterranian hypertensives and (2) to study their relationship with the risk of future stroke and cognitive decline.

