### Baseline visit and procedures

#### Inclusion and exclusion criteria

At inclusion visit, fulfilment of inclusion and exclusion criteria is re-assessed by investigators. Briefly, inclusion criteria consists on: 1)Patients with essential hypertension diagnosed at least one year earlier; 2) Age comprised between 50 and 70 years; 3) Patients who give their consent to participate in the study.

Patients are excluded when: 1) they have history of previous stroke or dementia; 2) Brain MRI is contraindicated; 3) there is a suspicion of white coat hypertension syndrome or 4) patients affected by a terminal illness preventing future follow-up examinations, based on the investigator criteria.

A particular effort is made to rule out the presence of a previous stroke, and for that purpose investigators are trained and an adaptation of the Stroke Symptom Questionnaire by Berger K and collaborators is used [9].

Likewise, when a suspicion of dementia appears, following DSM-IV-R criteria [10] the patient is not included in the study and a proper evaluation in the presence of a caregiver is therefore recommended.

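### The ±2-point accuracy rests on a 10% prevalence from population-based studies; in an all-hypertensive cohort it has almost no margin and should be stated over a range of prevalences

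*Protocol article*

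**What the plan says.** The Statistical methods section of the protocol article says the sample size "has been estimated using data of population-based studies published before, which reported specific data on silent brain infarcts prevalence in participants aged 50 to 70". It continues: "According to them, the expected prevalence should be about 10" per cent. From this it concludes that, "with a confidence interval of 95% and an accuracy of 2%, sample size should be of at least 865 individuals". The figure is then raised to 1000 for possible losses. No accuracy is given at any other prevalence.

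The inclusion criteria admit only "Patients with essential hypertension diagnosed at least one year earlier", so the whole cohort is hypertensive. The Abstract says that silent infarcts "increase significantly both with advancing age and hypertension", and the Background section repeats this. The Background also says that studies in hypertensive participants "reported a prevalence of silent brain infarcts that ranges from 20 to 86% of subjects aged 40 to 88 years old". It adds at once that most of these studies were in Japanese populations and that Mediterranean data are limited.

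**The concern.** The planning value and the study population are matched on age but, as far as the text shows, not on hypertension. The article names hypertension as a factor that raises the prevalence of silent infarcts, and it does not explain why a population-based figure should apply to hypertensives. The planning value is half the lowest figure it reports for hypertensives.

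This matters because, below 50%, the half-width of the interval for a proportion widens as the proportion rises. If prevalence lies above the planning value, which is the direction the article's own reasoning points to, the interval will be wider than stated. Prevalence of silent infarcts and other silent lesions is listed first among the primary outcomes, and its precision is the only basis given for the sample size.

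**Working it through.** **Inputs.** From Statistical methods: prevalence p = 0.10, 95% confidence (z = 1.96), half-width d = 0.02, n = 865, raised to 1000. From Background: 20 to 86% in hypertensives aged 40 to 88. From Subject selection: about 27000 eligible people.

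**Reproducing the plan's figure.** With the usual (Wald) formula, n = z² p(1−p) / d² = 1.96² × 0.10 × 0.90 / 0.02² = 864.4, which rounds up to 865. This is an exact match. The step to 1000 corresponds to a loss of 13.5%, since 1000 × (1 − 0.135) = 865.

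**Half-width at other prevalences.** Half-width = 1.96 × √(p(1−p)/n). For example, at p = 0.20 and n = 865: 1.96 × √(0.16/865) = 0.0267. The last column is the number needed for ±2 points.

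| Prevalence | 865 evaluable | 1000 evaluable | n for ±2 points |
|---|---|---|---|
| 10% | ±2.00 | ±1.86 | 865 |
| 15% | ±2.38 | ±2.21 | 1225 |
| 20% | ±2.67 | ±2.48 | 1537 |
| 30% | ±3.05 | ±2.84 | 2017 |
| 50% | ±3.33 | ±3.10 | 2401 |
| 86% | ±2.31 | ±2.15 | 1157 |

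The half-width peaks at 50% and falls on either side. Since ±2 points is missed at both 20% and 86%, it is missed everywhere between them, even with no losses.

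**Highest prevalence at which ±2 points still holds (below 50%).** Solve p(1−p) = n d² / z².

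- n = 865: p(1−p) = 865 × 0.0004 / 3.8416 = 0.0901, so p = 10.0%.
- n = 1000: p(1−p) = 1000 × 0.0004 / 3.8416 = 0.1041, so p = 11.8%.

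**Allowing for the finite population.** With N = 27000 and n = 1000, the variance is multiplied by (27000 − 1000)/(27000 − 1) = 0.963. The limit becomes p(1−p) = 0.1041 / 0.963 = 0.1081, so p = 12.3%. At 20% the number needed falls from 1537 to 1536.6 / (1 + 1535.6/27000) = 1453.9, that is 1454. The correction helps a little and does not change the picture.

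**The case against.** The strongest reply is that the article claims nothing false. The accuracy is derived from an expected prevalence of 10%, and at that prevalence 865 does give ±2.00 points and 1000 gives ±1.86. A reader might infer an arithmetic error in the sample size; there is none.

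A reader might also infer that prevalence in this cohort must be 20% or more, or that 10% is a floor. The documents do not support either. The 20 to 86% range spans ages 40 to 88, and age is the other driver that the article names; the studies were mainly Japanese. ISSYS enrols Mediterranean patients aged 50 to 70 without previous stroke or dementia. The article gives no size for the effect of hypertension in that age group. The studies behind the 10% are not at hand, so whether they already allow for hypertension cannot be checked. The imaging definition is also restrictive: it requires cerebrospinal fluid signal in all sequences and a rim on FLAIR, and does not count lesions in the lower third of the basal ganglia. A figure carried over from other studies could therefore be off in either direction.

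Finally, the loss is small. No test, power claim or decision threshold depends on ±2 points, and the final interval will show its own width. Relative precision even improves: 2.00/10 is 20% of the estimate, while 2.67/20 is about 13%.

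All of this stands, and it limits the point. It does not remove it. The concern does not need a prevalence of 20%: a rise from 10% to 12% already exceeds the limit with all 1000 evaluable under the formula the plan uses. That rise is in the direction the article says hypertension pushes, and scarce Mediterranean data are a reason to show a range instead of one value.

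**Conclusion.** The point holds as a minor to moderate weakness in a planning assumption. The sample size is computed correctly for a prevalence of 10%, but the article does not show that 10% suits a cohort made up entirely of hypertensives, and the accuracy has almost no margin above it. The ±2 points hold up to a prevalence of 10% with 865 evaluable and about 11.8% with 1000 (about 12.3% with the finite-population correction). They are missed throughout the range the article reports for hypertensives. At 20% the excess is about half a point with 1000 evaluable (2.48 − 2.00 = 0.48) and 0.67 with 865.

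A reader might go further and conclude that the study is too small or that its prevalence estimate is compromised. Neither follows. The shortfall depends on a true prevalence that is not known at planning, and a wider interval is still a valid one. The figures assume a simple random sample, the usual normal-approximation interval, and between 865 and 1000 evaluable participants.

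**What to change.** Keep 1000 participants and replace the single accuracy figure with a conditional statement, for example: 

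> With 1000 to 865 evaluable participants, the half-width of the 95% confidence interval is about 1.9 to 2.0 percentage points if prevalence is 10%, 2.2 to 2.4 if it is 15%, and 2.5 to 2.7 if it is 20%. The 10% is taken from population-based studies and may be low for hypertensives.

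If the source studies give a figure for hypertensives aged 50 to 70 that supports 10%, cite it in the same place.

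The cost is a change of wording in the sample-size paragraph and a slightly less favourable stated precision. No extra participants and no change of design are needed.

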## Methods/Design

ISSYS (Investigating Silent Strokes in Hypertensives: a magnetic resonance imaging study) is an observational cross-sectional and longitudinal study aimed to determine the prevalence of silent cerebrovascular lesions in a large cohort of hypertensives and to study their associated factors.

On baseline all participants will be also tested to determine other than brain (vascular, kidney, heart) organ damage, in order to establish the contribution of other subclinical conditions to global vascular risk.

Follow-up is planned to last for at least 3 years, to assess the rate of further Stroke/TIA and cardiovascular events as well as cognitive impairment, and their predictors.

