**Figure 1 F1:**
[figure not shown]
ISSYS procedures and outcomes for baseline and follow-up visits.

After inclusion, the participant is asked about demographical and personal medical history. Briefly, demographical information includes age, gender, ethnicity, current or former occupation, and the maximum educational level (or completed years of schooling) achieved by the patient.

Regarding medical history, the participant is asked about the duration of hypertension, the presence of other vascular risk factors such as diabetes mellitus, hyperlipidemia, alcohol intake (grams per week), smoking habit (current, former, never) and family history of premature vascular disease and dementia in first grade relatives.

Also a directed questioning is performed to assess for the existence of an established cardiovascular, kidney or systemic disease, together with the history of retinal abnormalities or the presence of a sleep apnea syndrome. Global vascular risk is calculated applying the SCORE risk charts and Framingham-calibrated REGICOR function when appropriate [11,12].

Data concerning ambulatory and home blood pressure, home medication and treatment adherence is collected. To evaluate treatment adherence, the validated questionnaire published by Morisky and collaborators [13] is used. Briefly, this scale was developed to assess treatment compliance in hypertension and currently is used in many other chronic conditions. It consists in 4 questions, with yes/no answers which should be asked along the clinical interview, and reflect the patient’s attitude towards treatment. It is useful to find out whether or not the patient is a good complier and the causes for non-adherence.

Finally, the clinical interview ends with two self-administered questionnaires assessing life-style habits (physical activity and diet). Physical activity is evaluated by means of the International Physical Activity Questionnaire (IPAQ) [14] and dietetic habits are evaluated with a short questionnaire on frequency of dietary intake [15].

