## Discussion

Silent brain infarcts have been recently included into the new definition of stroke, given that their high prevalence and clinical consequences, such as further strokes and cognitive decline do not support to treat them as innocent findings anymore.

Although it is known that silent infarcts are associated with age and vascular risk factors, particularly hypertension, there is limited information on the prevalence of this condition in our setting. Studies restricted to hipertensives participants have been performed mainly in Asian populations and they are mostly cross-sectional, with no prospective follow-up to address either the incidence of new lesions on imaging or the presence of future strokes or cognitive decline.

ISSYS is designed to investigate both the prevalence of silent brain infarcts and the incidence of strokes, cognitive decline and appearance of new brain infarcts after three years of follow-up in a cohort of 1000 Mediterranian hypertensives.

Moreover, we will study the risk factors associated with their presence and the relationship between them and other hypertensive target organ damage, such as those occurring in heart, kidney or vessels, in order to know their single and combined contribution to the global vascular risk in each patient.

Hopefully, the better knowledge on the frequency and determinants of these lesions will help in the future to optimize treatments or establish new preventive strategies to minimize clinical and socioeconomic consequences of stroke and dementia.

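### The stated Cox analysis only partly answers the contribution-to-risk aim: it does not ensure adjustment for the calculated SCORE/REGICOR risk and names no joint test of the markers

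*Protocol article*

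**What the plan says.** **The aim.** The Methods/Design introduction says organ damage outside the brain is measured at baseline "in order to establish the contribution of other subclinical conditions to global vascular risk". The Abstract says much the same, with the risk of further vascular events as the target. The Discussion goes further: it takes silent infarcts together with damage to heart, kidney and vessels, "in order to know their single and combined contribution to the global vascular risk in each patient".

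**The risk measure.** Under Clinical data collection: "Global vascular risk is calculated applying the SCORE risk charts and Framingham-calibrated REGICOR function when appropriate". REGICOR appears once more, under Preventive treatments during follow-up, where it identifies high-risk participants. No stated analysis uses either score.

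**The analysis.** Statistical methods gives one model for follow-up events: "Cox proportional hazards multivariate analysis will be used to identify clinical predictors of stroke/TIA or further CVE". It is to be "adjusted by variables showing p values <0.1 on univariate testing". The output is fixed too: "Results will be shown as OR or HR, as appropriate, with their corresponding 95% confidence intervals".

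**The concern.** The aim has two parts: what each marker contributes to a risk that the study already quantifies, and what the markers contribute together. The stated model is not tied to either part.

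- **Reference risk.** A hazard ratio shows a contribution beyond established risk only if established risk is in the model. Here the adjustment set is whatever passes a univariate screen in these data. The score, or some of its components, may or may not be included.
- **Joint contribution.** The same screen can remove a marker before the markers are considered together, and no test of the set is named.

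At stake is the interpretation of the result. A significant hazard ratio adjusted for an incidental set of covariates could be taken to show that brain imaging or vascular testing adds to the score. Conversely, several modest markers that jointly carry information could each fail the screen and never be examined as a set.

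**Working it through.** **1. The plan's own figure.** The only sample-size calculation is for prevalence: 10% expected, 95% confidence, precision of 2 percentage points.

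n = 1.96² × 0.10 × 0.90 / 0.02² = 864.3, rounded up to 865.

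This reproduces the stated 865, which was raised to 1000 for losses. It is correct for prevalence. It was not derived for any event analysis, and the article gives no event rate.

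**2. Aim against analysis.**

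| Element of the aim | What Statistical methods fixes | Match |
|---|---|---|
| Contribution of a single marker | Hazard ratio from a multivariable Cox model | Partial: an adjusted association, with an adjustment set chosen by the data |
| Relative to global vascular risk as calculated (SCORE/REGICOR) | Nothing requires the score or its components in the model | Not ensured |
| Combined contribution (Discussion only) | No joint test named; screening comes first | Partial: joint association can be derived only for markers that survive |

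**3. How often the screen would drop a real marker.** Inputs: prevalence 0.10 (the protocol's expected prevalence of silent infarcts); 1000 participants; assumed proportions with an event of 1%, 3%, 5% and 8%, giving D = 10, 30, 50 and 80 events; assumed true hazard ratios of 2 and 3; a two-sided test, since sidedness is not stated.

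Formula (Schoenfeld approximation): z = √(D × 0.10 × 0.90) × ln(HR). Chance of passing p < 0.1 in the true direction = Φ(z − 1.645).

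With D = 30 and HR 2: z = √2.7 × 0.693 = 1.139, and Φ(1.139 − 1.645) = Φ(−0.506) = 0.306.

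| Events | Passes screen, HR 2 | Passes screen, HR 3 |
|---|---|---|
| 10 | 0.162 | 0.273 |
| 30 | 0.306 | 0.564 |
| 50 | 0.431 | 0.754 |
| 80 | 0.585 | 0.904 |

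At 30 events a marker that truly doubles the hazard would be dropped about 69% of the time (1 − 0.306).

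**4. What the event count allows.** For 80% power at two-sided 0.05 and 10% prevalence, D = (1.960 + 0.842)² / (0.09 × ln(HR)²). This gives 182 events for HR 2.0, 104 for HR 2.5 and 73 for HR 3.0. With 30 events the power is about 21% for HR 2 and 44% for HR 3. A joint model with the score, silent infarct and four organ-damage markers, one parameter each, has 6 parameters, so 30 / 6 = 5 events per parameter. This limits what any analysis can show and favours summarising established risk in one covariate.

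**The case against.** The strongest reply has four parts.

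- **A condensed article.** C-index, calibration and nested-model details commonly sit in a full protocol or analysis plan, which is not shown. This stands: their absence is no error, and the point does not rest on it. It rests on the adjustment rule and output that the article does state.
- **The aims are narrower.** The numbered aims in the Abstract and Background are prevalence and the relationship with future stroke and cognitive decline, for which an adjusted hazard ratio is a normal answer. Only the Discussion speaks of single and combined contribution, and no sentence promises a test of added value over the score. This also stands. However, the contribution aim is in the Abstract and Methods too, and the article itself uses the term global vascular risk for SCORE/REGICOR.
- **The Cox model does give an answer.** Mutually adjusted hazard ratios estimate single associations, and their product gives the joint association if effects multiply. The score can enter under the p < 0.1 rule. Correct, but neither is assured.
- **Few events.** Measures of added value would be very imprecise. This stands and shapes the fix.

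A reader might infer that the question is left entirely unanswered, or that the plan is defective because it reports no gain in discrimination. The documents support neither. Simulation does show that a 10%-prevalence marker with HR 2 raises the C-index by only about 0.006 to 0.012 (assuming 3% risk, independence from the score and a base C-index of 0.67 to 0.76). That mainly reflects how insensitive the C-index is, and is not evidence of an error in the plan.

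**Conclusion.** The point holds in limited form. The contribution aim is stated, the risk score is collected, and the only event analysis fixed neither ensures adjustment for that score nor tests the markers jointly. The aim is partly answered: single associations will be estimated, and joint ones can be derived for markers that survive screening.

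The size depends on an event rate that the article does not give. Across assumed three-year proportions of 1% to 8%, a 10%-prevalence marker with a true hazard ratio of 2 passes the screen with probability of about 0.16 to 0.59. These figures assume proportional hazards, a two-sided screen and no loss to follow-up. This is a worthwhile improvement to a stated rule. It invalidates neither the prevalence objective nor the Cox model as a measure of association.

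**What to change.** In Statistical methods, for participants to whom the score applies, specify a fixed sequence of Cox models:

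1. Log-transformed REGICOR (or SCORE, one chosen in advance) forced in as a single continuous covariate.
2. Add silent infarct.
3. Add each organ-damage marker singly: pulse wave velocity, ankle-brachial index, urine albumin-to-creatinine ratio, left ventricular hypertrophy.
4. Add the markers jointly, without univariate screening.

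Report the likelihood-ratio test for each addition and for the joint addition beside the hazard ratios and their 95% confidence intervals. Report any change in C-index, optimism-corrected and with its interval, only as exploratory. Limit the parameters in the joint model if events are few, for example about 30 if 3% of 1000 have an event.

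**Cost.** A few sentences and a little more analysis; the score and all the markers are already collected. Participants without an applicable score drop out of this sequence. Intervals will be wide, and the resulting claim may be less favourable than a hazard ratio alone would suggest.
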